## Efficacy Evaluation Method

### Tumor evaluation based on RECIST v1.1

In this study, RECIST v1.1 is used to evaluate the tumor response of subjects.

Selection criteria of target lesions: At the premise of no more than 2 target lesions per organ and no more than 5 total lesions, more organs with tumor involvement should be covered as far as possible. The number of target lesions, site description, long diameter of each target lesion (except lymph nodes), short diameter of lymph node lesions, and the sum of diameters of all lesions are recorded at baseline.

In particular, it should be noted that if gastric lesions need to be selected as target lesions, imaging should be performed at baseline and follow-up when the degree of gastric distension is the same.

Baseline and post-treatment efficacy assessments should be performed using the same method and by the same investigator whenever possible.

### Pathological efficacy evaluation

The surgical specimens are preserved and processed, and the pathological efficacy is assessed according to the TRG scoring criteria; the degree of eradication and ypN staging were assessed according to the AJCC Version 8;

Pathological response evaluation: Based on surgically resected primary lesions, the sites of assessment should include all primary lesions seen by imaging before neoadjuvant therapy, and sections with possible residual tumor cells should be selected for assessment. Viable tumor cells are defined as cells with the ability to proliferate and are graded as follows:

Pathological response evaluation criteria (TRG scoring criteria)*

| Grade 0 (Complete regression) | No viable tumor cells seen under light microscope (including lymph nodes, staging ypT0N0M0) |
| --- | --- |
| Grade 1 (well regression) | Single cell or small clusters of tumor cells scattered through fibrosis |
| Grade 2 (partial regression) | Fibrosis predominates, outgrowing residual tumor |
| Grade 3 (no regression) | Extensive residual tumor, no or little tumor cell necrosis |
| *Remarks: 1) TGR score is limited to the primary tumor bed;  2) Tumor cells refer to viable tumor cells, excluding degenerative and necrotic cells;  3) Large acellular mucinous lakes may appear after radiotherapy/chemotherapy and cannot be considered as residual tumor. | |

Major pathological response is defined as a grade greater than or equal to 1, i.e., grade 0, 1.

## Safety Evaluation

### Surgical safety

Including 30-day operative mortality, operative complication rate (surgical site infection, anastomotic leakage, gastrointestinal bleeding, incision dehiscence, adhesive intestinal obstruction, biliary fistula and chylous fistula, fever of unknown origin with body temperature ≥ 37.5℃, etc.), reoperation rate, hospital stay, operation time.

### Adverse Event

The evaluation of AEs includes type, incidence, severity (graded according to NCI-CTCAE v5.0), onset and end time, whether it is an SAE and the correlation and outcome.

# Adverse Event Reporting

## Adverse events (AE)

### Definition of Adverse Events

An adverse event is any untoward medical occurrence in a clinical trial subject who has signed informed consent form (ICF). It may be any unfavorable and unintended symptom, sign, laboratory abnormality, or disease, but it does not necessarily have to have a causal relationship with this treatment. In this trial, any adverse medical events occur from the time the subject signs the informed consent form to 30 days after treatment are collected and followed up until the adverse event is relieved or stable. Adverse events include the following:

1) Worsening of preexisting (before entering the clinical trial) medical conditions/diseases (including worsening of symptoms, signs and laboratory abnormalities);

2) Any new adverse medical conditions (including symptoms, signs and newly diagnosed diseases);

3) Clinically significant abnormal laboratory values or results that are not attributable to concurrent illness.

The investigator shall record in detail any adverse event occurred to the subject, including: name of adverse event, description of all related symptoms, occurrence time, severity, correlation with the investigational drug, duration, actions taken for the investigational drug, final result and outcome.

### Criteria for determining the severity of adverse events

Refer to NCI-CTCAE 5.0 grading criteria for adverse drug events. For adverse events not listed in the table of NCI-CTCAE 5.0, the following criteria can be referred to:

| **Level** | **Clinical Description of Severity** |
| --- | --- |
| 1 | Mild; asymptomatic or mild symptoms; clinical or diagnostic observations only; intervention not indicated. |
| 2 | Moderate; minimal, local or noninvasive intervention indicated; limiting age-appropriate instrumental activities of daily living (instrumental ADL, referring to preparing meals, shopping for groceries or clothes, using the telephone, managing money, etc.) |
| 3 | Severe or medically significant but not immediately life-threatening; hospitalization or prolongation of hospitalization indicated; disabling; limiting self care ADL. Self care ADL refer to: bathing, dressing and undressing, feeding self, using the toilet, taking medications, and not bedridden. |
| 4 | Life-threatening consequences; urgent intervention indicated |
| 5 | Results in death |

### Criteria for judging the relationship between adverse event and study drug

The collection of adverse events begins from the time of informed consent and continues through the end of the safety follow-up period. All adverse events must be collected and reported in the form of clinical report, regardless of the relationship between the event and investigational drug and whether the drug is used or not. Any discomfort or abnormal changes in objective laboratory test indicators complained of during treatment should be recorded truthfully, and the severity, duration, treatment measures and outcome of adverse events should be indicated. The investigator should comprehensively determine the relationship between adverse events and the investigational drug, such as whether the occurrence of adverse events has a reasonable time sequence with the medication, the characteristics of the investigational drug, the toxicological and pharmacological effects of the investigational drug, whether the subject uses other concomitant drugs, the subject's underlying diseases, medical history, family history, and challenge and rechallenge reactions. The possible association between adverse events and investigational drug is evaluated according to the five-level classification of "definitely related, possibly related, possibly unrelated, definitely unrelated and indeterminable".

## Serious Adverse Event (SAE)

### Definition of Serious Adverse Event

An SAE refers to any medical event that occurs during the course of a clinical trial and requires inpatient hospitalization or prolongation of existing hospitalization, causes disability/incapacity, jeopardizes work ability, is life-threatening or results in death, or causes congenital anomaly, etc. It includes the following medical events:

- Events resulting in death;
- Life-threatening event (defined as an event in which the subject is at immediate risk of death);
- Events requiring inpatient hospitalization or prolongation of existing hospitalization;
- Events which can result in permanent or significant disability/incapacity or jeopardize work ability;
- A congenital anomaly or birth defect;
- Other important medical events (defined as an event which jeopardizes the subject or requires intervention to prevent any of the conditions listed above).

### Hospitalisation

Adverse events that result in hospitalization (even if less than 24 hours) or prolonged hospitalization in a clinical study should be considered serious.

Hospitalization does not include the following:

• Rehabilitation facility

• Nursing home

• Routine emergency room admission (less than 24 hours)

• Day surgery (e.g. outpatients/day/ambulatory surgery)

• Social reasons (medical insurance reimbursement, etc.)

Hospitalization or prolongation of existing hospitalization that is unrelated to the deterioration of an AE is not an SAE itself. For example:

- Hospitalization due to underlying disease, without the occurrence of any new AE or aggravation of underlying disease (e.g.for the purpose of investigating lab abnormalities existing before the trial and up to now);
- Hospitalization for administrative reasons (e.g.routine annual physical examination);
- Hospitalization which occurs in the clinical trial period and is specified in the trial protocol (e.g.: procedure per trial protocol);
- Elective hospitalization unrelated to deterioration of AE (e.g.elective plastic surgery);
- Predetermined treatment or surgical procedure should be recorded in the entire trial protocol and/or subject’s personal baseline data.
- Hospitalization for blood product use only.

Diagnostic or therapeutic invasive (e.g., surgical), non-invasive operations should not be reported as adverse events, but should be reported when the disease condition that leads to the procedure meets the definition of an adverse event. If acute appendicitis develops during the adverse event reporting period, it should be reported as an adverse event, and the resulting appendectomy should be recorded as the treatment for that adverse event.

### Disease progression and death

Disease progression is defined as the deterioration of a subject's condition caused by the indication for which the investigational drug is administered, including radiographic progression and progression of clinical symptoms and signs. Both the occurrence of new metastasis relative to the primary neoplasm and the progression of original metastasis are considered progressive disease. Any event which is life-threatening, requires inpatient hospitalization or prolongation of existing hospitalization, or results in permanent or significant disability/incapacity or jeopardizes work ability, or is a congenital anomaly/birth defect, and is caused by the signs and symptoms of progressive disease should not be reported as an SAE in an expedited manner. Death caused by the signs and symptoms of progressive disease should be reported an SAE in an expedited manner. If there is any uncertainty as to whether an SAE is due to disease progression, it should be reported as an SAE.

Disease progression is expected in this study population and the word "disease progression" cannot be reported as an AE term. When disease progression occurs, the event used to confirm disease progression should be reported as an AE. For example, if a subject has a seizure that is determined to be related to brain metastasis, the AE term should be recorded as "seizure" and not "disease progression" or "brain metastasis".

"Death" is not defined as an AE or SAE term, but should be recorded as the outcome of the event; the event that caused or contributed to death should be recorded as the AE or SAE. If the cause of death is unknown and could not be determined at the time of reporting, the AE or SAE term is recorded as "death of unknown cause".

### Reporting system of serious adverse events

It starts from signing of the informed consent until 30 days (inclusive) after the last dose of study drug. During the trial, in case of any serious adverse event, no matter initial report or follow-up report, the investigator should immediately report it to the relevant unit according to the regulatory requirements within 24 hours after being informed of the SAE.

For serious adverse events, the symptoms, severity, correlation with the investigational drug, time-of-onset, handled time, action taken, follow-up time and method, and outcome should be recorded in detail. All serious adverse events should be followed up until they disappear, resolve to baseline or ≤ Grade 1, or reach a stable state, or are reasonably explained, or subjects are lost to follow-up, or die.

Below is supplemental information that is included in BMS-Sponsored trials. It is the responsibility of the Sponsor-Investigator to determine if this information regarding hospitalization is considered SAEs or not and whether it should be included in the protocol.

- - a visit to the emergency room or other hospital department < 24 hours, that does not result in admission (unless considered an important medical or life-threatening event)
  - elective surgery, planned prior to signing consent
  - admissions as per protocol for a planned medical/surgical procedure
  - routine health assessment requiring admission for baseline/trending of health status (eg, routine colonoscopy)
  - Medical/surgical admission other than to remedy ill health and planned prior to entry into the study. Appropriate documentation is required in these cases.
  - Admission encountered for another life circumstance that carries no bearing on health status and requires no medical/surgical intervention (eg, lack of housing, economic inadequacy, caregiver respite, family circumstances, administrative reason).
  - Admission for administration of anticancer therapy in the absence of any other SAEs (applies to oncology protocols)

**NOTE**: Although pregnancy and potential drug-induced liver injury (DILI), are not always serious by regulatory definition, these events must be reported within the SAEs timeline.

**NOTE**: Any component of a study endpoint that is considered related to study therapy should be reported as an SAE (eg, death is an endpoint, if death occurred due to anaphylaxis, anaphylaxis must be reported).

The **causal relationship** to study drug is determined by a physician and should be used to assess all adverse events (AE). The casual relationship can be one of the following:

**Related**: There is a reasonable causal relationship between study drug administration and the AE.

**Not related**: There is not a reasonable causal relationship between study drug administration and the AE.

The term "reasonable causal relationship" means there is evidence to suggest a causal relationship.

An appropriate SAE form (e.g. ex-US = CIOMS form or USA = Medwatch form) should be used to report SAEs to BMS. If the Sponsor-Investigator prefers to a study specific/Institutional form, it must be sent to the BMS ISR Trial Manager prior to study initiation for internal BMS review to ensure that at a minimum all of the data elements on the CIOMS form are present.

Please include the BMS Protocol number on the SAE form or on the cover sheet with the SAE form transmission.

- - The CIOMS form is available at: <https://cioms.ch/cioms-i-form/>
  - The MedWatch form is available at: https://www.fda.gov/safety/medical-product-safety-information/medwatch-forms-fda-safety-reporting

**NOTE**: If a CIOMS I or Medwatch form is selected for reporting, the investigator causal assessment must be provided in the narrative section, otherwise the BMS form must be used.**NOTE**: For studies with long-term follow-up period in which safety data are being reported, include the definition of end date of SAE collection.

SERIOUS ADVERSE EVENT COLLECTION AND REPORTING

All Serious Adverse Events (SAEs) that occur following the subject’s written consent to participate in the study through *100* days of discontinuation of dosing must be reported to BMS Worldwide Safety, whether related or not related to study drug**. If applicable,** SAEs must be collected that relate to any follow-up protocol-specified procedure (eg, a follow-up skin biopsy).

- Following the subject’s written consent to participate in the study, all SAEs, whether related or not related to study drug, are collected, including those thought to be associated with protocol-specified procedures. The Investigator should report any SAE occurring after these aforementioned time periods, which is believed to be related to study drug or protocol-specified procedure.
- An SAE report should be completed for any event where doubt exists regarding its seriousness;
- If the Investigator believes that an SAE is not related to study drug, but is potentially related to the conditions of the study (such as withdrawal of previous therapy or a complication of a study procedure), the relationship should be specified in the narrative section of the SAE Report Form.

SAEs, whether related or not related to study drug, and pregnancies must be reported to BMS within 24 hours \ 1 Business Day of becoming aware of the event. SAEs must be recorded on either CIOMS, MedWatch, or approved study specifi/institutional SAE form.

**SAE Email Address:**  [contact]

**SAE [contact]

If only limited information is initially available, follow-up reports are required. (**Note**: Follow-up SAE reports should include the same investigator term(s) initially reported.)

If an ongoing SAE changes in its intensity or relationship to study drug or if new information becomes available, a follow-up SAE report should be sent within 24 hours \ 1 Business Day to BMS using the same procedure used for transmitting the initial SAE report.

All SAEs should be followed to resolution or stabilization.**NOTE:** The Sponsor-Investigator must provide a single centralized e-mail address (not an individual’s e-mail address) to be used by BMS to send AE/SAE report related queries. The single centralized e-mail address must be provided in the Study Contract and sent to [contact].

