# Study medication

## Overview of investigational product

In the study, study drugs are defined as Sintilimab.

|  | Sintilimab |
| --- | --- |
| Manufacturer | Innovent, China |
| Dose Form | Injection fluid |
| Strength | 100 mg |
| Route of Administration | Intravenous |

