**Expedited and periodic safety update reporting by BMS:**

It is the Sponsor-Investigator’s responsibility to report events to their Local HA. In addition, suspected serious adverse reactions (whether expected or unexpected) shall be reported by BMS to the relevant competent health authorities in all concerned countries according to local regulations (either as expedited and/or in aggregate reports).

In accordance with local regulations, BMS will notify Sponsor-Investigator of all reported SAEs that are suspected (related to the investigational product) and unexpected (ie, not previously described in the IB). An event meeting these criteria is termed a **Suspected, Unexpected Serious Adverse Reaction (SUSAR)**. Sponsor-Investigator notification of these events will be in the form of either a SUSAR Report or a Semi-Annual SUSAR Report. Sponsor-Investigator (or delegate) will receive these reports through the FastTrack portal.

Other important findings which may be reported by BMS as an Expedited Safety Report (ESR) include: increased frequency of a clinically significant expected SAE, an SAE considered associated with study procedures that could modify the conduct of the study, lack of efficacy that poses significant hazard to study subjects, clinically significant safety finding from a nonclinical (eg, animal) study, important safety recommendations from a study data monitoring committee, or Sponsor-Investigator or BMS decision to end or temporarily halt a clinical study for safety reasons.

Upon receiving an ESR from BMS, the Sponsor-Investigator **must review and retain the ESR with the IB**. Where required by local regulations or when there is a central IRB/IEC for the study, the Sponsor-Investigator will submit the ESR to the appropriate IRB/IEC. The investigator and IRB/IEC will determine if the informed consent requires revision. The investigator should also comply with the IRB/IEC procedures for reporting any other safety information.

NON-SERIOUS ADVERSE EVENT COLLECTION AND REPORTING

The collection of non-serious AE information should begin following the subject’s written consent to participate in the study. All non‑serious adverse events (not only those deemed to be treatment-related) should be collected continuously during the treatment period and for a minimum of 100 days following the last dose of study treatment.

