**Reporting**

Product Quality Complaints must be reported to BMS **within one (1) business day** of awareness to [**[contact]**](mailto:[contact])**.**

In the event of a suspected product quality issue, the affected product must be quarantined immediately at the Investigational site.

The affected product should not be disposed unless retention presents a risk to personnel (e.g., cytotoxic, risk of injury from broken glass or sharps).

When reporting, as much product information as possible should be reported. At a minimum, but not limited to, include:

- ISR Study number, site reference, product description, impacted batch number, container number(s), photographs, and any other supporting information

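### Section 7.2.4 names BMS as the company for safety reporting and quality complaints, while Section 5.1 names sintilimab, made by Innovent, as the only study drug, and no route to or from Innovent is stated

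*Protocol*

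**What the plan says.** Section 5.1 (Overview of investigational product) is unambiguous about the drug: "In the study, study drugs are defined as Sintilimab". The table below that sentence gives the maker as "Innovent, China". That is the only mention of Innovent in the protocol. The Protocol Summary names a hospital as sponsor.

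Section 7.2.4 (Reporting system of serious adverse events) opens with a general duty: for any SAE "the investigator should immediately report it to the relevant unit according to the regulatory requirements within 24 hours after being informed of the SAE". The unit is not named. A list of hospitalisations follows, introduced by "Below is supplemental information that is included in BMS-Sponsored trials", with a remark that the Sponsor-Investigator must decide whether the list belongs in the protocol.

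From there on the text is specific and mandatory, and the company it names is BMS. All SAEs from consent onwards "must be reported to BMS Worldwide Safety, whether related or not related to study drug". The same section directs pregnancies, aggregate non-serious events, three-monthly case reconciliation and product quality complaints to BMS. It expects SUSAR notices and expedited safety reports (ESRs) to come from BMS. An event counts as unexpected on the test "unexpected (ie, not previously described in the IB", and the protocol does not say whose investigator's brochure (IB) this is.

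**The concern.** The reporting chain is written around one company and the study drug comes from another. Site staff follow instructions of this kind literally and under time pressure. As written, they owe a report within 24 hours or one business day to a company with no stated link to the drug, and they have no stated duty towards its maker.

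Three practical things are at stake:

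- **Expectedness.** The judgement whether a serious reaction is unexpected needs an identified reference document for sintilimab. None is identified.
- **Incoming safety information.** Section 7.2.4 makes ESRs the trigger for deciding whether the informed consent needs revision. The protocol expects them from a company that it does not show to be connected with sintilimab.
- **Product quality.** A suspected defect in a sintilimab vial has no complaint route under the stated definition.

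**Working it through.** No arithmetic applies. The check is to trace each flow in Section 7.2.4 and compare its named party with Section 5.1 and the Protocol Summary.

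| Flow | Party named | Place in Section 7.2.4 |
|---|---|---|
| SAEs, outgoing | BMS Worldwide Safety, within 24 hours or one business day | Serious adverse event collection and reporting |
| Pregnancies, outgoing | BMS | Same part; also Pregnancy |
| Non-serious events, aggregate, outgoing | BMS | Non-serious adverse event collection and reporting |
| Case reconciliation, every 3 months | BMS pharmacovigilance | Adverse event reconciliation process |
| Product quality complaints, outgoing | BMS, for BMS products only | Product quality complaints |
| SUSAR notices, incoming | BMS | Expedited and periodic safety update reporting |
| ESRs, incoming | BMS | Same part |
| SAEs, general duty | Unnamed unit, within 24 hours | Opening paragraph |
| Events to the authority | Local health authority | Expedited and periodic safety update reporting |
| ESRs passed on; other safety information | IRB/IEC | Same part |
| Any flow to or from Innovent | None stated | None |

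**Step 1: direction.** Five flows go out to BMS (SAEs, pregnancies, aggregate non-serious events, reconciliation, quality complaints). Two come in from BMS (SUSAR notices, ESRs). Three routes involve neither BMS as recipient nor Innovent: the unnamed unit, the local health authority and the IRB/IEC.

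**Step 2: link between company and drug.** No section says that BMS makes, supplies or distributes sintilimab, or sponsors this trial. Section 5.1 and the Protocol Summary name other parties for manufacture and sponsorship.

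**Step 3: quality complaints.** The definition covers products made or distributed by BMS, by third parties under contract with it, or for it. Nothing in the protocol places Innovent in such an arrangement. On the document's own wording, a sintilimab complaint therefore falls outside the definition: the route is absent rather than merely misdirected.

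**Step 4: is this deliberate or carried over?** The signs point to carry-over. The hospitalisation list is labelled as coming from BMS-sponsored trials. A later part on special situations still carries a drafting note telling the author to delete what does not apply. Nivolumab, which is not a study drug here, survives in the dose-modification heading and in the tests required during the treatment period. The two layers of Section 7.2.4 also disagree on the SAE window: 30 days after the last dose in the opening paragraph, 100 days after dosing stops in the BMS text. That disagreement needs reconciling in its own right.

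**The case against.** The strongest reply is that the protocol does not depend on BMS alone. The opening of Section 7.2.4 already requires SAE reports within 24 hours under regulatory requirements, the Sponsor-Investigator must report events to the local health authority, and IRB/IEC procedures apply. Adverse event capture (Sections 6 and 7.1) does not run through BMS, and immune-toxicity management rests on a named guideline. The text also refers to a study contract and an agreement that are not shown, and these could give BMS or Innovent a defined role. Title and contact details were removed from the copy reviewed.

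Much of this stands, and it rules out several stronger readings that a reader might infer:

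- *All safety reporting runs to BMS.* It does not, given the three other routes above; and SUSAR notices run from BMS, not to it.
- *Sintilimab safety signals never reach its maker.* The protocol states no route to Innovent. The unnamed unit, the authority or an unseen agreement could still lead there.
- *BMS holds no data on sintilimab, supplies the IB, or would send SUSARs about another product.* The documents say none of this. The SUSAR text refers to the investigational product and to an IB without naming its source.
- *The protocol itself doubts whether the whole BMS text belongs.* The remark about inclusion concerns only the hospitalisation list.

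What the reply does not remove is the mismatch between Sections 5.1 and 7.2.4. None of the surviving routes identifies a reference safety document for sintilimab, a source of incoming sintilimab safety information, or a place to send a sintilimab quality complaint.

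**Conclusion.** The point holds as an internal contradiction in operative safety text. Seven flows (five outgoing, two incoming) name BMS, none names the maker of the only study drug, and the quality-complaint definition excludes sintilimab as the protocol describes it. The instructions are mandatory and wrong as written. This is more than a missing detail or a slip of wording, because staff who follow them would send reports to a company with no stated role.

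The effect is on the safety-reporting chain. The primary endpoint, the sample size and the collection of adverse event data are untouched, and local reporting duties survive.

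The conclusion rests on two assumptions: that no removed page or unseen contract gives BMS a role in sintilimab or in this trial, and that Section 5.1 is right about the drug and its maker. If the first fails, the protocol should still state the role and give the sintilimab route.

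**What to change.** Reconcile Sections 5.1 and 7.2.4 in one amendment:

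1. Replace the BMS recipients with this trial's actual chain: investigator to sponsor, ethics committee, competent authority and the manufacturer named in Section 5.1. Name the unit that the opening paragraph leaves open.
2. Identify the sintilimab IB or label as the reference for expectedness, and state from whom SUSAR notices and ESRs on sintilimab will come.
3. Define product quality complaints for sintilimab and name their recipient.
4. Name the counterpart for case reconciliation.
5. If BMS does have a role, state what it is and for which product, and still add the sintilimab route.
6. Remove the remaining drafting notes.

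The cost is a protocol amendment, which needs ethics committee approval under Section 8.2, and a safety contact arrangement with the manufacturer. No patient procedure is added.
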